## 12.4 Other variables

Demographic data (age, gender, weight, body mass index (BMI))

Surgery related data (duration of surgery and anesthesia, precise classification of surgical procedure)

Concomitant medication/therapy on ICU (see NOTE above)

## 12.5 Source Documents

For definitions of source data and source documents see 17.1.

The following table represents the source documents for the data to be entered in the CRF:

| Variable                                                                                | Source document                                                        |
|-----------------------------------------------------------------------------------------|------------------------------------------------------------------------|
| Informed consent                                                                        | Informed consent form, patient chart                                   |
| Patient's data (demographics: sex, age, indication, concomitant diseases, history etc.) | Patient chart (ethnicity CRF)                                          |
| Exclusion criteria that refer specifically to the placement of the Doppler tube         | Study specific working sheet                                           |
| ASA                                                                                     | CRF                                                                    |
| Weight (measured)                                                                       | CRF                                                                    |
| Pre-operative measures (questioning of patient)                                         | CRF                                                                    |
| IAD                                                                                     | CRF                                                                    |
| Indication                                                                              | Anaesthesia chart                                                      |
| Description of procedure                                                                | CRF                                                                    |
| Investigational Product administration                                                  | Intraoperative and postoperative charts, study specific working sheet  |
| Concomitant medication                                                                  | Intraoperative and postoperative charts                                |
| Haemodynamics                                                                           | Intraoperative and postoperative charts, study specific working sheets |
| Laboratory measures                                                                     | Laboratory print-out                                                   |
| Aldrete Score, NuDesc, fit-for-discharge criteria                                       | CRF                                                                    |
| PONV                                                                                    | CRF                                                                    |
| Nutrition intake (questioning of patient) and gastrointestinal parameters (time         | CRF                                                                    |

| Variable                                                                                               | Source document                                               |
|--------------------------------------------------------------------------------------------------------|---------------------------------------------------------------|
| until first flatus, time until full oral nutrition, first bowel movement, time until first defaecation |                                                               |
| Adverse events                                                                                         | Intraoperative and postoperative charts, patient chart
CRF |
| HRQoL                                                                                                  | Questionnaire                                                 |
| Final assessment                                                                                       | CRF                                                           |
| Study termination                                                                                      | CRF, patient chart                                            |

### 13 ASSESSING AND REPORTING OF ADVERSE EVENTS

Throughout the course of the clinical trial particular attention is paid to Adverse Events and Adverse Drug Reactions.

#### 13.1 Definitions

##### 13.1.1 Adverse Events

An Adverse Event (AE) is any untoward medical occurrence in a patient or clinical investigation subject administered a pharmaceutical product and which does not necessarily have a causal relationship with this treatment. An AE can therefore be any unfavourable and unintended sign (including an abnormal laboratory finding), symptom, or disease temporally associated with the use of an Investigational Product, whether or not related to the Investigational Product or study treatment/procedures.

##### 13.1.2 Adverse Reaction

Adverse Reactions (AR) are all untoward and unintended responses to an Investigational Product related to any application / dose administered. All adverse events judged by either the reporting investigator or the sponsor as having a reasonable causal relationship to a medicinal product qualify as AR. The expression reasonable causal relationship means to convey in general that there is evidence or argument to suggest a causal relationship.

Regarding marketed Investigational Products: a response to a product which is noxious and unintended and which occurs at applications normally used in man for prophylaxis, diagnosis, or therapy of diseases or for modification of physiological function.

##### 13.1.3 Unexpected Adverse Reactions

An AR, the nature or severity of which is not consistent with the applicable product information ( = reference document, e. g. Investigator's Brochure (IB) for an unauthorised Investigational Product or SmPC for an authorised product).

When the outcome of the AR is not consistent with the applicable product information this AR should be considered as unexpected.

The applicable product information/reference document in the present study is the SmPC as identified in section 19.9.

### 13.1.4 Serious Adverse Event (SAE) or Serious Adverse Reaction (SAR)

Any untoward medical occurrence or effect that at any dose

- Results in Death
- Is life threatening
- Requires hospitalisation or prolongation of existing inpatients' hospitalisation
- Results in persistent or significant disability or incapacity
- Is a congenital anomaly or birth defect

More than one of the above criteria can be applicable to the one event.

#### NOTE:

**Death:** is the outcome of an SAE. The event to be reported comprehensively is the medical condition leading to death, e.g. underlying disease, accident.

**Life-threatening:** in the definition of a SAE or SAR refers to an event in which the patient was at risk of death at the time of the event; it does not refer to an event which hypothetically might have caused death if it was more severe.

**Hospitalisation** is defined as inpatient care of more than one calendar day (overnight admission). Admission for ambulant diagnostic procedures, overnight survey visits or ambulant visits to an emergency ward, e. g. during weekends are not considered 'hospitalisation' in the sense of the criteria for SAE / SAR, unless any of the other criteria for serious is met.

Medical judgement should be exercised in deciding whether an AE / AR is serious in other situations. Important: AEs / ARs that are not immediately life-threatening or do not result in death or hospitalisation but may jeopardise the patient or may require intervention to prevent one of the other outcomes listed in the definition above, should also be considered serious.

### 13.1.5 Adverse Event Intensity

| Intensity | Definition                                                                      |
|-----------|---------------------------------------------------------------------------------|
| Mild      | Patient is aware of signs and symptoms but they are easily tolerated            |
| Moderate  | Signs / symptoms cause sufficient discomfort to interfere with usual activities |
| Severe    | Patient is incapable to work or perform usual activities                        |

Cave: The term "severe" is often used to describe the intensity (severity) of a specific event. This is not the same as 'serious', which is based on patient/event outcome or action criteria (see definition 11.1.4)!

### 13.1.6 Adverse Event Causality

| Causality code | Definition                                                                                                                  |
|----------------|-----------------------------------------------------------------------------------------------------------------------------|
| Not assessable | A report suggesting an AE, which cannot be judged because information is insufficient or contradictory, and which cannot be |

|          |                                                                                                                                                                                                                                                                                                                                                                                                                                                        |
|----------|--------------------------------------------------------------------------------------------------------------------------------------------------------------------------------------------------------------------------------------------------------------------------------------------------------------------------------------------------------------------------------------------------------------------------------------------------------|
|          | supplemented or verified.                                                                                                                                                                                                                                                                                                                                                                                                                              |
| Unlikely | A clinical event, including laboratory test abnormality, with a temporal relationship, which makes a causal relationship improbable, and in which other drugs / treatments, chemicals or underlying disease(s) provide plausible explanations.                                                                                                                                                                                                         |
| Possible | A clinical event, including laboratory test abnormality, with a reasonable temporal relationship to administration of the drug / treatment, but which also could be explained by concomitant diseases or other drugs / treatments or chemicals.                                                                                                                                                                                                        |
| Probable | A clinical event, including laboratory test abnormality, with a reasonable temporal relationship to administration of the drug / treatment, unlikely to be attributable to concomitant disease(s) or other drugs / treatments or chemicals, and which follows a clinically reasonable response on withdrawal (dechallenge). Rechallenge information is not required to fulfil this definition.                                                         |
| Certain  | A clinical event, including laboratory test abnormality, occurring in a plausible time relationship to study treatment and which cannot be explained by concomitant disease(s), other drugs / treatments or chemicals. The response to withdrawal of the treatment (dechallenge) should be clinically plausible. The event must be unambiguously either pharmacologically or as phenomenon, using in satisfactory rechallenge procedures if necessary. |

## 13.2 Recording and Reporting Adverse Events and Adverse Reactions

### 13.2.1 Recording

The Investigator must record in detail all AEs (signs and symptoms) which are either volunteered by patients or observed during or following the course of Investigational Product administration and during the course of the study on the appropriate CRF page.

Included in the description should be

- the nature of the sign or symptom;
- the date of onset; date of resolution (duration);
- the severity / intensity (for definition see section 13.1.5);
- the investigator's judgement on possible relationship to study treatment or other therapy (for definition see section 13.1.6);
- the action taken (if any), and
- the outcome.

During surgery and during stay on ICU several events including deviation from normal laboratory values occur which are events due to underlying disease and treatment and are therefore, not considered to be adverse events. This includes e. g. the specified use of inotropes in order to keep the patient hemodynamically stable, the use of specified amount of blood products in order to replace surgically caused blood loss, specified insulin treatment for blood sugar control on ICU, pre-specified increase in body temperature within a specified time period after surgery, etc. The pre-specified events, laboratory deviations respectively time points and periods are listed in detail in appendix 10. This list is to be used in order to harmonize adverse event reporting during this multicentric study. Nevertheless, concomitant medication and reason for it will be documented as described in section 11.

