#### Blood and lymphatic system disorders

**Tetraspan:** Very common: Decreased haematocrit and reduced concentration of plasma proteins due to dilution. Common (depending on the administered dose): Relatively large doses of hydroxyethyl starch result in dilution of coagulation factors and can therefore affect blood coagulation. Bleeding time and aPTT can be prolonged and the level of FVIII/vWF complex can be reduced after administration of large doses.

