## **23 APPENDICES**

- 1 Declaration of Helsinki (*version dated 1996*)
- 2 Patient Information Sheet and Informed Consent Form
- 3 Screening Log
- 4 Enrolment Log
- 5 Randomisation Sheet
- 6 Dosing Algorithm
- 7 Inventory Form
- 8 NuDesc and Scores, Fit for Discharge-criteria
- 9 Serious Adverse Event Form

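### Section 13.2.1 takes peri-operative laboratory deviations out of adverse event recording without requiring that they be unrelated to the study product, and leaves the limits to an appendix the protocol does not list

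*Protocol*

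**What the plan says.** Section 13.1.1 defines an AE broadly. It can be any "unfavourable and unintended sign (including an abnormal laboratory finding), symptom, or disease temporally associated with the use of an Investigational Product", related to the product or not.

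Section 13.2.1 then narrows what is recorded. It refers to several events during surgery and ICU stay, expressly including departures from normal laboratory values, "which are events due to underlying disease and treatment and are therefore, not considered to be adverse events". The examples carry qualifiers. The blood-product example, for instance, is "the use of specified amount of blood products in order to replace surgically caused blood loss". The list of examples is open-ended. For the limits the section says: "The pre-specified events, laboratory deviations respectively time points and periods are listed in detail in appendix 10". It gives the purpose of that list as uniform AE reporting across centres, and adds that concomitant medication and the reason for it are still documented.

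The appendix list in the table of contents and the one in section 23 both end with item 9; in section 23 the last entry reads "9 Serious Adverse Event Form".

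Section 13.4 lists the known Tetraspan reactions. Under blood and lymphatic disorders it gives decreased haematocrit and plasma proteins as very common. It gives dilution of coagulation factors as common and dose-dependent, adding: "Bleeding time and aPTT can be prolonged and the level of FVIII/vWF complex can be reduced after administration of large doses". Raised serum amylase is listed as very common under laboratory investigations.

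**The concern.** The exclusion turns on attribution to disease and treatment, and treatment is not restricted to treatment other than the study product. The section nowhere says that an event thought to be related to the product stays an AE. The limits that might have said so are not in the protocol.

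The excluded class, laboratory deviations during surgery and ICU stay, is also the class that holds most of the HES reactions in section 13.4. If such findings are set aside before any causality judgement, the AE and adverse reaction tables could under-report the effects that are specific to the products under study. Centres could also apply the exclusion differently, because each would have to supply its own limits.

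**Working it through.** The point rests on no rate, alpha or sample size, so the check is a comparison of sections.

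1. **Definition against exclusion.** Section 13.1.1 admits an abnormal laboratory finding as an AE whatever its cause. Section 13.2.1 removes some abnormal laboratory findings because of their presumed cause. The two rules give different answers for the same finding. Section 9.4.3 follows the broad rule: it gives clinically significant abnormal laboratory values as an example of AEs that may lead to withdrawal.

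2. **Causality grading against exclusion.** In section 13.1.6 an event with another explanation is kept and graded. The grade Possible covers an event with a reasonable time relation "but which also could be explained by concomitant diseases or other drugs / treatments or chemicals"; Unlikely covers events where other causes are the plausible explanation. Under section 13.2.1 the same competing explanation takes the event off the AE page, so no grade is assigned.

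3. **Consequence for adverse reactions.** Section 13.1.2 builds adverse reactions from AEs judged to have a reasonable causal relationship. An event that is not recorded as an AE receives no such judgement and cannot enter the adverse reaction count.

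4. **The limits.** Appendices in the table of contents: 9. Appendices in section 23: 9. Appendix cited in section 13.2.1: 10. The qualifiers in section 13.2.1 (a specified amount, a pre-specified increase) therefore have no content in the protocol.

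5. **Overlap with known reactions.** Decreased haematocrit, prolonged aPTT, reduced FVIII/vWF and raised amylase are all laboratory deviations. Hypersensitivity and itching, also in section 13.4, are not and are not touched. The red-cell trigger in section 11 is a haematocrit below 25%, and section 13.4 says HES lowers haematocrit by dilution. Transfusion for surgical loss and transfusion prompted by dilution are thus hard to tell apart when the exclusion is applied.

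6. **What is still captured.** Section 12.2 and the laboratory table in section 14.2 set against the reactions:
   - aPTT, vWF and ROTEM: baseline to the morning of postoperative day 1 (ROTEM also one hour into surgery).
   - FVIII:c and fibrinogen: baseline and end of surgery only.
   - Haematocrit: with the blood gases during surgery and on ICU.
   - Blood products are recorded; blood loss is measured intraoperatively.
   - Amylase: not scheduled.

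   The exclusion covers the whole ICU stay and AEs are recorded to day 5, so the scheduled coagulation tests do not span the same period. Scheduled values also carry no causality or seriousness judgement.

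**The case against.** The strongest reply is that section 13.2.1 is narrower than it first looks. It covers several events, not all laboratory deviations. Its examples are qualified, and none of the section 13.4 reactions is named as excluded. Replacing surgical blood loss is not the same thing as dilutional coagulopathy. If nothing has been pre-specified, one may even argue that nothing is excluded and section 13.1.1 governs. All of this is fair as far as it goes. It shows that the reactions may be dropped, not that they must be. It does not resolve the conflict, since the section asserts that an exclusion is in force and gives no rule that keeps product-related events in.

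Serious events are largely protected. Section 13.1.4 defines them independently of section 13.2.1. Section 13.2.2 requires all of them to be reported, related or not, and the few types exempt from expedited reporting are still fully documented on the AE form. This stands.

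A reader might infer four stronger things that the document does not support:

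- *That a HES patient with dilutional coagulopathy and transfusion would necessarily have no AE on record.* The qualifiers in section 13.2.1 do not allow that.
- *That appendix 10 does not exist.* It is not among the nine listed appendices, but a separate document cannot be ruled out.
- *That the study-level stopping criterion is disabled.* Section 9.4.1 concerns serious adverse reactions only, and non-serious laboratory dilution does not feed it.
- *That an ongoing comparison between arms is diluted.* Section 19.1.3 appoints no DSMB and section 16.6 plans only a blinded variance estimate, so any effect falls on the final tables.

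**Conclusion.** The concern holds in a limited form. Sections 13.1.1, 13.1.6 and 13.2.1 cannot all be applied as written to a peri-operative laboratory deviation, and the text meant to set the boundary is not in the protocol. Non-serious, laboratory-type HES reactions may be left out of the AE and adverse reaction tables before anyone has judged causality.

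No size can be put on this. How much is excluded depends on a list that is not available. Section 13.4 gives one frequency statement for Tetraspan covering both the 10% and the 6% product, so it supplies no difference between the two HES arms. Any figure for attenuation would be invented.

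The loss is partial, because most of the affected quantities can still be compared between arms as laboratory or transfusion data. The gaps are coagulation after the morning of day 1, amylase, and the missing causality judgement. The point matters more than a wrong cross-reference, because repairing the reference alone would still leave an exclusion with no stated condition on causality. The conclusion assumes that any separate list adds no such condition; if it does, what remains is to bring that condition into the protocol.

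**What to change.** Reconcile sections 13.1.1, 13.2.1 and 13.4 with one paragraph in section 13.2.1:

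- An event is exempt from AE recording only if it is on the pre-specified list, is not serious, and is judged not related to the study product.
- Any listed event that is serious, or is judged at least Possible on the scale in section 13.1.6, is recorded as an AE.

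Add the list as a numbered appendix, included in the table of contents and section 23, or correct the reference to wherever it is kept.

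The cost is that paragraph and the appendix. The downside is some additional AE forms for expected peri-operative findings, and a relatedness judgement on listed events that investigators might otherwise have passed over.

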### 13.2.2 Reporting of Serious Adverse Events and Unexpected Adverse Reactions

All SAEs (for exemptions see below), whether or not deemed Investigational Product-related or expected must be reported to the Sponsor by telephone within 24 hours (one working day) of the Investigator becoming first knowledge:

Contact Name: see "Responsibilities and Addresses (section 1)

A written report must follow within five working days and is to include a full description of the event and sequelae, in the format detailed by the Serious Adverse Event reporting form provided by the Sponsor (see appendix 9).

The Sponsor will notify the competent authorities, IECs and all investigators concerned of suspected ARs which are unexpected (SUSARs) in line with pertinent legal requirements.

While reporting adverse events, all pertinent data protection legislation must be adhered to.

Exemptions from expedited reporting: SAEs that are known for the indication respectively the surgery have not to be reported on an expedited basis but will be fully documented on the AE-CRF-page. In detail, the following SAEs are exempted from expedited reporting: Anastomotic insufficiency, Re-intubation, re-do surgery, (not bleeding), postoperative delir.

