### 9.4.1 Discontinuation Criteria Related to the Study

Criteria for discontinuation / termination of the entire clinical study include (not exclusively)

- Unexpected high frequency of serious adverse reactions during the study (frequency as outlined in SmPC will serve as a basis).
- Occurrence of a suspected unexpected serious adverse reaction which does not justify a continuation of the study
- Patients cannot be recruited in sufficient numbers. Not sufficient is defined as recruitment of less than 4 patients per month on average in all participating centres.

If after pilotphase (after 60 patients) the calculation of the pooled variance reveals that the estimated total number of 228 patients will be exceeded the study will not be carried on but stopped for futility after the pilot phase (see section 16).

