### **19.9 Completion of Case Report Forms**

Any data to be recorded directly on the CRFs (to be considered as source data) will be defined at the start of the study (see section 12.5).

For paper CRFs all entries should be made in black ink for duplication purposes. The investigator must ensure the accuracy, completeness, legibility and timeliness of data reported in the CRF and all required reports.

In case electronic CRFs (remote data entry) are used the investigator must strictly adhere to the written instructions of the respective software description.

Any change or correction to a CRF must be dated, initialled and explained (if necessary) and must not obscure the original entry, this applies to both written and electronic changes.

For the present study considerations regarding the use of electronic CRFs are made. In case this applies, the software of the CRO as mentioned in section 1 in the current available version will be used. Details on the software and version number will be compiled in a separate document prior to start of the study and filed in the study files.

Data reported on the CRF that are derived from source documents should be consistent with the source documents or the discrepancies should be explained.

For paper CRFs the Investigator should agree to have completed and signed CRFs available for full inspection by the clinical monitor within two weeks after completion of each patient.

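### The exemption from 24-hour SAE reporting goes by event type with no causality condition, so a related case of, for example, anastomotic insufficiency or delirium reaches the sponsor late

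*Protocol*

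**What the plan says.** Protocol 13.2.2 sets a general rule: "All SAEs (for exemptions see below), whether or not deemed Investigational Product-related or expected must be reported to the Sponsor by telephone". A written account comes next: "A written report must follow within five working days". The section then exempts certain events: "SAEs that are known for the indication respectively the surgery have not to be reported on an expedited basis". The list reads "Anastomotic insufficiency, Re-intubation, re-do surgery, (not bleeding), postoperative delir". These events are to be documented on the adverse event page of the CRF. The same section commits the sponsor to notify authorities, ethics committees and investigators of SUSARs and makes no exception for the listed events.

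Three other parts of the protocol bear on this:

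- **Expectedness.** Section 13.1.3 defines an unexpected adverse reaction as "An AR, the nature or severity of which is not consistent with the applicable product information". Sections 13.1.3 and 19.8 name the SmPC as the reference.
- **Stopping the study.** One criterion in 9.4.1 is "Occurrence of a suspected unexpected serious adverse reaction which does not justify a continuation of the study". Another is an unexpectedly high frequency of serious adverse reactions, with the SmPC frequencies as the basis.
- **CRF timing.** Section 19.9 asks that completed paper CRFs be "available for full inspection by the clinical monitor within two weeks after completion of each patient". It gives no deadline for entry into an electronic CRF, which is only under consideration.

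Section 19.1.3 states that no DSMB will be appointed.

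**The concern.** The exemption and the SUSAR duty use different tests. The exemption asks whether an event is known for the operation or the indication. The SUSAR duty asks whether a reaction judged related is consistent with the SmPC. An event can be familiar after pancreatic head surgery and still be unexpected for the product. When the investigator attributes such an event to the infused fluid, the text still sends it to the CRF alone.

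The sponsor's obligation to notify then depends on information that the protocol allows to arrive weeks later. Section 13.1.2 also lets the sponsor judge causality itself, which it cannot do for an event that it has not received. The two safety criteria in 9.4.1 draw on the same information, and no independent board reviews safety data in the meantime.

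**Working it through.** The protocol states no figure to reproduce. The check is a comparison of sections, followed by a simple estimate of the delay.

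**1. Scope of the exemption.** It is carved out of a rule that applies whatever the causality or expectedness. The criterion is the type of event, and no causality condition appears. The words in brackets after re-do surgery most naturally keep re-do surgery for bleeding under 24-hour reporting.

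**2. Are the listed events expected?** Section 13.4 summarises these reactions from the SmPCs:

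- Tetraspan: haemodilution, effects on coagulation, anaphylactoid and hypersensitivity reactions, itching, raised amylase.
- Sterofundin ISO: water and electrolyte overload, hypersensitivity, paralytic ileus, reactions linked to the infusion technique.

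None of the four listed events is named. For anastomotic insufficiency and delirium nothing in the summary comes close. Re-intubation is less clear, because it could follow overload or an anaphylactoid reaction, both of which are described.

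**3. Consequence.** Take a serious case of anastomotic insufficiency or delirium that the investigator rates *possible* on the 13.1.6 scale. By 13.1.2 it is an adverse reaction. By 13.1.3, on the summary in 13.4, it is unexpected. By 13.2.2 the sponsor must notify it, yet 13.2.2 also exempts it from the 24-hour call.

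**4. Length of the delay, paper CRF.**

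- The patient's study ends on postoperative day (POD) 15 or at discharge, whichever is first (15.1). Latest: day 15.
- The CRF is due 14 days after completion (19.9): 15 + 14 = day 29.
- Adverse events are recorded until POD 5 (12.2). Event on POD 1: 29 − 1 = 28 days. Event on POD 5: 29 − 5 = 24 days.

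The limit for other SAEs is 24 hours.

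**5. Patients enrolled meanwhile.**

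- Planned accrual is 228 patients (16.4) in 2 years (15.2): 228 / 24 = 9.5 per month, or 228 / 730 = 0.312 per day.
- 24 × 0.312 = 7.5 and 28 × 0.312 = 8.7, so about 7 to 9 patients.

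**6. A separate, minor point on the clock.** For SAEs that are not exempt, the event "must be reported to the Sponsor by telephone within 24 hours (one working day) of the Investigator becoming first knowledge". An event learned of late on a Friday is due on Saturday under the first limit (about 24 hours) and on Monday under the second (about 72 hours).

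**The case against.** The case for leaving the text alone has substance. The four events are systematically collected anyway: surgical complications and delirium scores are secondary efficacy variables in 12.3, and the synopsis requires re-intubation to be documented. Exempting common surgical complications from telephone reports is a sensible way to limit workload. The investigator records causality for every adverse event (13.2.1), monitors visit at regular intervals and verify source data (18.1.2), and any code break because of an SAE must be reported promptly (9.5). All of this stands, and it means that the information is delayed rather than lost. It does not supply the missing causality condition. The protocol does not state the interval between monitoring visits, and the code-break route works only if the code is broken.

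A reader might infer more than the protocol supports:

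- **That every related case is certainly a SUSAR.** The full SmPCs are not at hand, and 13.4 is a summary that itself refers to further SmPC text on overdose. Re-intubation after fluid overload is a poor example, because overload is described in 13.4 and 14.4 and such a case could be argued to be expected.
- **That the stopping criteria cannot work, or that nobody sees these events.** The criteria in 9.4.1 are expressly not exhaustive, one of them concerns a cumulative frequency, and monitoring and the CRF still deliver the data.
- **That the delay exceeds three months.** This would require completion to mean the 3-month call. Section 15.1 ends the patient's study at POD 15 or discharge, and 14.1 describes the later contact as a telephone call for quality of life only.
- **That leakage is a designated safety objective.** Section 7.2 lists it among safety and efficacy parameters together, and 12.3 places it under efficacy.

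**Conclusion.** The point holds in a limited form. As written, 13.2.2 exempts listed events even when they are judged related to the product, and this conflicts with the SUSAR duty in the same section. Anastomotic insufficiency and delirium are the clearest cases.

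The effect is a delay of up to about 24 to 28 days for an event on POD 1 to 5, with about 7 to 9 further patients enrolled, where other SAEs are telephoned within 24 hours. These are upper figures. They assume a paper CRF, no discharge before POD 15, no earlier monitoring visit and accrual at the planned rate. Earlier discharge, a monitoring visit or an electronic CRF would shorten the delay, but no stated deadline guarantees it. The classification as unexpected rests on the summary in 13.4.

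The sponsor may have meant to exempt only cases attributed to the surgery. The text does not say so, and sites will follow the text. The primary analysis is not affected. What is at stake is timely SUSAR notification and timely input to the safety criteria in 9.4.1, in a trial without a DSMB.

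**What to change.** In 13.2.2, limit the exemption to listed events that the investigator judges *unlikely* to be related to the Investigational Product. State that a listed event judged *possible*, *probable*, *certain* or *not assessable*, or one that is fatal, is reported within 24 hours like any other SAE. The sponsor's own causality judgement on events rated *unlikely* would still wait for the CRF, which is the price of keeping an exemption at all.

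As a separate tidy-up, remove the reference to one working day so that a single 24-hour clock applies, weekends included.

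The change is short, but under 19.7 it needs a signed amendment, prior documented ethics committee approval and submission to the competent authorities. Sites would also have to be told, and would complete a few more expedited forms. The workload purpose of the exemption survives, because listed non-fatal complications judged unlikely to be related stay exempt.
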